#### Sample size {14}

To facilitate aims 1 and 2, GLM will be utilized, which is a flexible generalization of ordinary linear regression that allows for response variables that have error distribution models other than a normal distribution and is often robust to smaller sample sizes. With a sample size of *n* = 30 at 80% power and *α* = .05, we should be able to detect a moderate-to-large overall model effect (*f*^2^ = 0.45), while including all three in-socket mechanics. We will examine the effect(s) of each in-socket mechanical parameter on outcomes by utilizing the type III sum of squares tables. If our sample size drops below 30, we will develop separate models for each of the parameters of interest and outcome.

For aim 3, in order to compare the two methods of socket design (the quantitative design method compared to standard of care), we will compare patient-reported outcomes and cost between the two methods, utilizing the Wilcoxon-Mann-Whitney non-parametric test. With a sample size of *n* = 15 at 80% power and *α* = .05, we will be adequately powered to detect a moderate-to-large effect (*d* = 0.476) with respect to the differences in patient-reported outcomes and cost by method.

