## Statistical methods

### Statistical methods for primary and secondary outcomes {20a}

#### Aim 1

The effects of in-socket mechanics, such as residual bone motion, peak skin strain, and pressure distribution on both physical function and patient-reported outcomes will be assessed using a generalized linear model (GLM). We will examine the effect(s) of each in-socket mechanical parameter on outcomes by utilizing the type III sum of squares tables. If our sample size drops below 30, we will develop separate models for each of the parameters of interest and outcome. Finally, we will create a unified model, containing the statistically significant parameter coefficients, which will allow us to predict physical function and patient response based on the changes to the included parameter estimates.

#### Aim 2

We will use partial correlation to examine the association between residual femur motion, skin strain, pressure, and readily available clinical measurements, while adjusting for potential confounders such as residual femur length (derived from CT data), overall residual limb length (measured from ischial tuber to distal end of the limb by caliper), contraction potential (tape measured as the difference of circumferential volumes during thigh muscle contraction and relaxation), and soft-tissue coverage (measured as a ratio between thigh and femur diameter). Partial correlation is a measure of the strength and direction of a linear relationship between two continuous variables whilst controlling for the effect of one or more other continuous variables (also known as “covariates” or “control” variables). Although partial correlation does not make the distinction between independent and dependent variables, the two variables are often considered in such a manner (i.e., you have one continuous dependent variable and one continuous independent variable, as well as one or more continuous control variables). If data is not approximately normal, we will use log transformations. Moderate-to-strong, significant correlations between research-grade and clinical data will be retained for empirical testing in aim 3.

#### Aim 3

Statistical analysis for aim 3 will involve two parts. First, the predictive model developed in aims 1 and 2 will be tested using data from 15 new participants (i.e., data not used to create the model). Second, we will compare the quantitative socket design to the current standard of care, in terms of patient outcomes and cost.

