As part of the pilot clinical trial, we will use empirical data to test the socket modification model(s) created in aim 1 and clinical measure correlations obtained in aim 2. When empirical data are used to evaluate the model, there are several conventional statistical tests that can be applied to test the null hypothesis that the model output is wrong. These involve showing that some form of the predicted value does not equal the same form of the observed value (e.g., typical predicted, typical observed). The simplest empirical comparison is that of a regression of observed values on predicted values. We will obtain data as described for aims 1 and 2 on an additional 15 transfemoral prosthesis users using their current sockets and the sockets designed as part of the standard of care and through the new quantitative design process.

In order to compare the two methods of socket design (the quantitative design method compared to Standard of Care), we will compare patient-reported outcomes and cost between the two methods, utilizing the Wilcoxon-Mann-Whitney non-parametric test. Socket Comfort Scores (SCS, a simple patient-reported comfort score from 0 to 10) will be used to evaluate patient outcomes after wearing the two sockets. The SCS are reported to have a standard deviation of 2.3 points [50], meaning we will be powered to detect a difference of 1.1 points in the SCS given our sample size. With regard to costs, we will compare the two design approaches on the number of visits, cost of materials, and total cost of labor needed to develop the new socket. These costs will be recorded by the study prosthetist in his practice for the standard of care and in the Biodynamics Lab for the quantitative design method.

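### The aim 3 model validation states its test backwards: showing that predictions differ from observations supports the stated null that the model is wrong and cannot reject it

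*Protocol article*

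**What the plan says.** The protocol article's section on statistical methods for primary and secondary outcomes {20a} splits the aim 3 analysis into two parts. In the first, "the predictive model developed in aims 1 and 2 will be tested using data from 15 new participants". The second compares the two socket design methods.

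For the first part, the article says that conventional tests can be used to "test the null hypothesis that the model output is wrong. These involve showing that some form of the predicted value does not equal" its observed counterpart. The first of these two sentences sets the null hypothesis, and the second says how the tests work. Next comes the only concrete analysis named for the validation: "The simplest empirical comparison is that of a regression of observed values on predicted values". No hypothesis for slope or intercept, no limit of agreement and no error measure is given with it.

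The 15 new participants are to be measured "using their current sockets and the sockets designed as part of the standard of care and through the new quantitative design process", so there are three sockets per person. The aim 3 power statement in Sample size {14}, which begins "With a sample size of *n* = 15 at 80% power and *α* = .05", concerns the comparison of the two design methods. No power or precision is stated for the validation.

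**The concern.** A test rejects its null hypothesis when the data are hard to reconcile with that null. If the null is that the model output is wrong, the evidence against it must be that predicted and observed values are close. The article offers the reverse, a demonstration that they are unequal. That demonstration can only add support to the null as stated.

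Two repairs come to mind, and neither gives a validation rule as the text stands. If the null is turned round to predicted equals observed, the test can expose a bad model, but a non-significant result does not establish a good one. If the null is kept, rejecting it needs a stated limit within which predictions count as close enough, and there is none.

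This matters because the validation is half of the aim 3 analysis, and the data-informed design process described under Specific aim 3 rests on this predictive model. An analysis plan that took over the hypothesis wording would take over the error too.

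**Working it through.** **1. The logic, side by side.**

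| | Null hypothesis | Evidence that rejects it | What non-rejection shows |
|---|---|---|---|
| As written | Model is wrong | Said to be: predicted ≠ observed (this supports the null) | Undefined |
| Conventional difference test | Predicted = observed | Predicted ≠ observed | Not agreement |
| Equivalence form | Difference of at least a margin | Difference shown to be inside the margin | Agreement not shown |

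Only the third row can reject a null that the model is wrong, and it needs a margin. The first row fails at any sample size. There is no plan figure to reproduce here, because none is stated for the validation.

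**2. Illustration: how often a difference test at n = 15 finds a biased model.** Assumptions not in the documents: one value per person, normal prediction errors, two-sided 5% paired t test, bias δ in units of the SD of the prediction error. The noncentrality is δ√15, with 14 degrees of freedom and critical value 2.145.

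- δ = 0.3: noncentrality 1.16, power 19%
- δ = 0.5: noncentrality 1.94, power 44%
- δ = 0.7: noncentrality 2.71, power 71%
- δ = 0.8: noncentrality 3.10, power 82%

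A mean bias of 0.5 SD therefore goes undetected 100 − 44 = 56% of the time.

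**3. The regression under its two usual tests, n = 15, one value per person (simulated, 40,000 runs).**

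- *Joint test of intercept 0 and slope 1.* Unbiased predictions unrelated to outcome are rejected 14%, 32% and 55% of the time when the prediction SD is 0.3, 0.5 and 0.7 of the outcome SD. They survive about 86%, 68% and 45% of the time, against 95% for a perfectly calibrated model.
- *Test of slope = 0.* Take predictions correlated 0.7 with outcome but spread 2.5 times as widely as the outcome, so that the true slope is 0.7/2.5 = 0.28 instead of 1. The slope is significant about 88% of the time. Association is shown and the miscalibration is missed.
- *Smallest correlation with 80% power for slope = 0* (Fisher z): tanh[(1.960 + 0.842)/√12] = 0.67. At a correlation of 0.5 the power is 48%.

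**4. Precision of the calibration slope.** For a calibrated model with correlation R, the 95% half-width is about t(0.975, 13) × √(1 − R²)/(R√14). With R = 0.5 this is 2.160 × 0.866/(0.5 × 3.742) = 1.00, so the interval runs from about 0 to 2. With R = 0.7 the half-width is 0.59.

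**5. The equivalence form** (two one-sided 5% tests, true difference zero, n = 15, simulated). Power is 15% for a margin of 0.476 SD of the prediction error, 43% for 0.6 SD and 81% for 0.8 SD. A confirmatory test of agreement is realistic only for a wide margin, which favours estimation.

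**6. How many values can inform the check.** The global rating of change is scored relative to the current socket (Plans for assessment and collection of outcomes {18a}), so it informs only the two new sockets: 15 × 2 = 30 values. PLUS-M is collected after each socket, and the in-socket measures are also taken in the current one, so these can use 15 × 3 = 45 values, clustered by person.

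**The case against.** The strongest reply is that this is one badly worded background sentence. The article says only that such tests can be applied. The analysis it actually names, regression of observed on predicted values in people not used to build the model, is sound. Slope and intercept hypotheses, intervals and error measures are commonly left to an analysis plan that is not shown. Aim 3 is described as a pilot, the trial as exploratory, and no power is claimed for the validation.

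Much of this stands. The regression is the right starting point, and the missing detail would not be a finding on its own. What does not fall to an analysis plan is a hypothesis and a method of testing it that are both stated and contradict each other.

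The reply also rules out several stronger readings:

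- A reader might infer that the study will declare the model validated on a non-significant difference or on any non-zero slope. The article states neither rule. The miss rates above describe what would happen if such a rule were adopted.
- A reader might blame the 15 participants. The reversal fails at any sample size; 15 makes the difference test weak and the intervals wide, but does not cause the error.
- A reader might conclude that nothing in the paragraph could validate the model. The regression could show association, or calibration if given a target and a limit.
- A reader might cap the usable data at 30 values. That holds only for the global rating of change.

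**Conclusion.** The concern holds as an error in the stated test logic: the null and the evidence said to count against it point in the same direction. This follows from the wording alone and needs no assumption.

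Its practical size is illustrative. With 15 participants, a mean bias of 0.5 SD of the prediction error is detected with about 44% power, and a calibrated model with correlation 0.5 has a slope interval of about 1 ± 1.0. These figures assume normal errors and one value per person. Using two or three sockets per person would help somewhat, by an amount that depends on the within-person correlation, which the documents do not give. The bias sizes are chosen for illustration, because the article gives no prediction-error SD.

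The documents do not support saying that the validation is bound to mislead or that the data cannot answer the question. The named regression can answer it in part if its results are reported as estimates. The correction should be made, since it changes what the first half of aim 3 may conclude.

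**What to change.** Replace the hypothesis wording in the aim 3 methods with estimation:

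- For each predicted outcome, regress observed on predicted values with errors clustered by participant: the global rating of change for the two new sockets; PLUS-M, function and in-socket measures for all three.
- Report the calibration intercept (target 0) and slope (target 1) with 95% confidence intervals.
- Report root mean squared error or mean absolute error, with an interval, against a predictor of no change or of the mean.
- State that a non-significant difference is not agreement, and that a slope different from 0 shows association, not calibration. A slope interval that excludes 0 should not serve as the criterion of success.
- Describe the validation as exploratory.

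The cost is a little more analysis on the same data and a less definitive statement about the model. No further participants or measurements are needed.

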#### Strategies to improve adherence to interventions {11c}

For aims 1 and 2, interventions (modified check sockets) will be administered only during data collection sessions in the lab. Study personnel will be present throughout those periods to respond to or prevent any issues, including a lack of adherence (i.e., participants doffing the socket during the test).

For aim 3, participants will be fitted with a new socket that will replace their original one on their regular prosthesis. The original socket will be retained at the prosthetist’s office to prevent unauthorized switching back by the participant or others. Participants will be asked to not use other prostheses they may own during the study period, and adherence to this will be evaluated by exit interviews.

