#### Participant timeline {13}

Participants in the first stage (aims 1 and 2) of the study, upon eligibility screening and completing the consent process, will be fitted for a check socket. After 4 weeks, during which time 8 derivatives of the socket will be produced, participants will complete testing with each of those socket variants over one or two lab visits. The participant timeline for the second stage (aim 3) includes clinical testing of one socket variant and spans a larger period (Fig. 8).

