#### Implementation {16c}

The allocation sequence will be generated by the study statistician who is not involved in the data collection. All participants in either study phase will be enrolled by the study PI and will eventually be exposed to all interventions of the study phase in a randomized sequential order.

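### Aim 3 names a test for independent samples, although the protocol mainly describes a within-person comparison of two sockets; the socket count per participant and the power claim also need restating

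*Protocol article*

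**What the plan says.** Statistical methods {20a}, aim 3, states: "we will compare patient-reported outcomes and cost between the two methods, utilizing the Wilcoxon-Mann-Whitney non-parametric test". The Abstract (Methods) and Sample size {14} name the same test.

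The same aim 3 text has 15 new prosthesis users provide data with their current socket, the standard-of-care socket and the quantitatively designed socket. It adds that Socket Comfort Scores (SCS) "will be used to evaluate patient outcomes after wearing the two sockets". Trial design {8} calls the study a single-group crossover. Implementation {16c} says participants in either phase "will eventually be exposed to all interventions of the study phase in a randomized sequential order".

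Two sections read differently. Participant timeline {13} says that the aim 3 timeline "includes clinical testing of one socket variant and spans a larger period". Strategies to improve adherence {11c} says that in aim 3 "participants will be fitted with a new socket that will replace their original one".

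On power, Sample size {14} claims 80% with n = 15 and α = 0.05 for the following: "moderate-to-large effect (*d* = 0.476) with respect to the differences in patient-reported outcomes and cost by method". The aim 3 text translates this into 1.1 SCS points at an SD of 2.3.

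**The concern.** The null variance of the Mann-Whitney statistic assumes that the two sets of scores are independent. If each person supplies both scores and the scores are positively correlated, that variance is too large for the comparison actually made. The test then rejects too rarely, both when there is no difference and when there is one. A real advantage of the new design method could be missed by the procedure meant to show it.

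The same test is planned for cost (visits, materials, labour), so the mismatch extends to those outcomes as well.

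The sections that suggest one new socket per person raise a second problem. Whether the test is wrong depends on the design, and the article does not describe the design consistently.

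**Working it through.** **Inputs from the protocol.** n = 15, power 80%, α = 0.05 and d = 0.476 (Sample size {14}); SD of the SCS 2.3 and detectable difference 1.1 points (Statistical methods {20a}). Sidedness, within-person correlation ρ, and whether 15 means pairs, total or per group are not given.

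**Step 1: the scale of d.** 0.476 × 2.3 = 1.095, which rounds to 1.1. So d is scaled by the SD of the score, not by the SD of within-person differences.

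**Step 2: the protocol's own power figure.** Noncentral-t power at d = 0.476:

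| Reading of n = 15 | Noncentrality | Two-sided | One-sided |
|---|---|---|---|
| 15 per group | 0.476 × √(15/2) = 1.30 | 24% | 35% |
| 15 in total, 7 and 8 | 0.476 × √(56/15) = 0.92 | 14% | 22% |
| 15 pairs, d in SDs of the difference | 0.476 × √15 = 1.84 | 40% | 54% |

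None of these readings gives 80%. A two-sample comparison would need 70 per group two-sided, or 55 one-sided. The value 0.476 does come out of a one-sided signed-rank calculation with 30 pairs (efficiency factor 3/π, power 79.95%). That is a paired test with twice the stated n, and the article does not say that this is the source.

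**Step 3: what pairing changes.** With score SD σ, the variance of the difference in means is 2σ²/n for independent groups and 2σ²(1 − ρ)/n for pairs. The SD of differences is 2.3 × √(2(1 − ρ)), which is 2.72 at ρ = 0.3, 2.30 at 0.5, 1.78 at 0.7 and 1.45 at 0.8.

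**Step 4: both tests on the same paired data.** Simulation with 15 pairs, bivariate normal scores, SD 2.3, a difference of 1.1 points, exact critical values and two-sided 0.05:

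| Assumed ρ | Mann-Whitney power | Signed-rank power | Share of power lost | Mann-Whitney type I error |
|---|---|---|---|---|
| 0 | 22% | 22% | none | 4.5% |
| 0.3 | 19% | 29% | about a third | 2.0% |
| 0.5 | 16% | 39% | about 60% | 0.8% |
| 0.7 | 12% | 58% | about 80% | 0.1% |
| 0.8 | 10% | 76% | nearly 90% | under 0.1% |

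Signed-rank type I error stays between 4.5% and 5% throughout. Other runs, or the normal approximation instead of exact critical values, move the powers by one or two percentage points.

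**Step 5: the correlation that the power claim would need.** A paired t-test on 15 pairs reaches 80% at 1.1 points only if ρ is about 0.81 two-sided (SD of differences 2.3 × √0.38 = 1.42) or 0.75 one-sided (2.3 × √0.50 = 1.63). At ρ = 0.8 Mann-Whitney gives about 10% two-sided and 25% one-sided.

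**The case against.** Aim 3 is presented as a pilot for preliminary evidence within an exploratory trial, and the error is conservative: it costs power and does not produce false claims of benefit. That is fair and limits the seriousness. It does not excuse the choice, because Sample size {14} calls the comparison adequately powered and Specific aim 3 states directional hypotheses.

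The one-socket reading can also be challenged. The timeline section points to a schedule figure that is not reproduced in the text available here. A new socket replacing the original one does not exclude two new sockets worn in turn. No section describes two groups, so a split of 7 and 8 is only what a literal one-socket reading would imply. This stands: it is an ambiguity to reconcile, not proof of a parallel design. If one socket per person were intended, Mann-Whitney would suit the design.

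A reader might infer that most of the power is lost in any case. The documents do not support that without a correlation: the loss is about a third at 0.3 and nil at zero. The figures above also cover comfort scores only. Cost is compared too, and the article gives nothing from which to size the effect there.

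**Conclusion.** The point holds in this form. As written, the named test does not match the within-person comparison set out in Statistical methods {20a}, Trial design {8} and Implementation {16c}. At the protocol's 1.1 points, more than half of the paired test's power is lost once the within-person correlation reaches about 0.5, and Mann-Whitney's true type I error is then below 1%. This rests on roughly normal scores, an SD of 2.3 for both sockets, a two-sided 0.05 level and an assumed correlation.

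A reader might also infer that a paired test would restore the stated 80%. It would not: signed-rank reaches about 39% at correlation 0.5 and about 76% at 0.8. The power claim is unsupported on every reading of n = 15 tried in step 2. If the sections suggesting one new socket were the intended design, the test would be appropriate, but power would be about 14% two-sided.

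**What to change.** 1. Reconcile Participant timeline {13} and Strategies to improve adherence {11c} with Implementation {16c} and the aim 3 analysis text, so that all state the same number of new sockets per aim 3 participant. Which design is meant is for the investigators to say.
2. Match the test to that answer. For the within-person design, replace Wilcoxon-Mann-Whitney in the Abstract, Sample size {14} and Statistical methods {20a} with a paired analysis, such as the Wilcoxon signed-rank test on within-participant differences, for both comfort and cost.
3. Restate the aim 3 power with sidedness, the meaning of n = 15 and an assumed SD of differences (or correlation) with a range. Otherwise drop the claim of adequate power and present aim 3 as estimation.

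Under the within-person design these are changes of wording and calculation, with no further participants or data. If one new socket per person is intended, Mann-Whitney can stay, but the design, allocation and analysis sections need rewriting and the power claim cannot stand with 15 people.

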#### Specific aim 3: Develop and evaluate an improved socket design and optimization process through the use of a predictive model based upon clinical measurements

In order to generate preliminary evidence on the clinical utility of the findings from aims 1 and 2, we will perform a pilot trial, using new subjects, to compare our data-informed optimization process resulting from aim 2 to the conventional iterative process for selecting a socket design and then optimizing the socket fit and function. We hypothesize that the data-informed method is advantageous in terms of (H1) patient-reported outcomes and (H2) cost, defined by the number of visits and socket iterations, and the amount of labor required to optimize the socket fit and function.

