**Fig. 6 Fig6:**
[figure not shown]
Flowchart showing the relationship between aims 1 and 2 (green background) and the pilot clinical trial, aim 3 (orange background). As an example, the flowchart shows three clinical measurements identified in aim 2 that correlate to in-socket mechanics obtained from research-grade measurements. In this example, those three clinical measures will then be used as predictors to guide the quantitative socket design

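### Aim 3 cost is analysed on a different list of components from the one H2 defines, and each method's cost is recorded in a different place, so H2 is only partly tested and monetary differences cannot be separated from setting

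*Protocol article*

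**What the plan says.** Under Specific aim 3, H2 concerns "cost, defined by the number of visits and socket iterations, and the amount of labor required to optimize the socket fit and function".

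In Statistical methods {20a}, Aim 3, the two design approaches are instead to be compared on "the number of visits, cost of materials, and total cost of labor needed to develop the new socket". The test is stated there as "we will compare patient-reported outcomes and cost between the two methods, utilizing the Wilcoxon-Mann-Whitney non-parametric test".

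The same paragraph fixes where the costs come from. They are "recorded by the study prosthetist in his practice for the standard of care and in the Biodynamics Lab for the quantitative design method".

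Two other places bear on the point. Implementation {16c} says participants in either phase will "eventually be exposed to all interventions of the study phase in a randomized sequential order". The Fig. 6 legend, giving an example with three clinical measures, says "those three clinical measures will then be used as predictors to guide the quantitative socket design".

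**The concern.** Cost is one of the two aim 3 hypotheses, it is part of the third study objective, and it is formally tested. Two features of the plan weaken that test.

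First, the hypothesis and the analysis list different components. The one that disappears, socket iterations, is the most direct measure of what the new process should improve. The Critical needs section describes present socket fitting as lengthy and repetitive, and the Objectives say the new process should expedite it. A reader of the results could be told that cost did or did not differ without ever seeing whether fewer iterations were needed.

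Second, each method's cost is recorded in its own place. A monetary difference could then reflect prices in the two places rather than the design method, and it could go in either direction. Changing labor from an amount to a cost increases this exposure, because hours carry no price.

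**Working it through.** **Step 1. Component lists side by side.**

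| Component | H2 (Specific aim 3) | Aim 3 analysis ({20a}) | Status |
|---|---|---|---|
| Visits | number | number | unchanged |
| Socket iterations | number | not listed | dropped |
| Labor | amount | total cost | unit changed |
| Materials | not listed | cost | added |

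Of the three H2 components, one carries over unchanged, one changes unit and one is lost. Of the three analysed components, two are monetary. The scope of labor also shifts, from optimizing fit and function in H2 to developing the new socket in the analysis.

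**Step 2. Can material cost stand in for iterations?** Not reliably. Under Modified brim height (aims 1 and 2), the protocol itself describes changing a socket by grinding down an existing copy. That is a modification that needs no new socket, so a count of iterations and a sum of material costs can move apart.

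**Step 3. Method against setting.** There are four possible combinations.

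| | Prosthetist's practice | Biodynamics Lab |
|---|---|---|
| Standard of care | recorded | not recorded |
| Quantitative method | not recorded | recorded |

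Only two of the four cells are filled, so method and setting are the same variable in the cost data. A larger sample does not separate them. Randomizing the order of sockets within a participant does not either, because the setting travels with the method. The planned Wilcoxon-Mann-Whitney test has no term for setting.

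**Step 4. How a price difference would enter.** Labor cost = hours × hourly rate. Comparing quantitative with standard of care:

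cost ratio = (hours ratio) × (rate ratio).

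With identical hours and a laboratory rate 20% higher (an assumption), the cost ratio is 1 × 1.20 = 1.20, all of it from the setting. With the same rate gap, a true saving in hours to 1/1.20 = 0.83 of standard of care would be hidden completely, since 0.83 × 1.20 ≈ 1. The same algebra applies to material prices. It does not apply to visits, iterations or hours.

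**Step 5. Illustration of size.** The protocol gives no rates, prices or cost variability, so every input here except n = 15 is assumed: log-normal labor cost, coefficient of variation 30%, within-person correlation 0.5, identical true hours, two-sided .05, 4,000 simulated trials per cell.

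| Assumed rate gap | Planned rank-sum test, p<.05 | Signed-rank test, p<.05 |
|---|---|---|
| 10% | about 6% | about 19% |
| 20% | about 31% | about 58% |
| 30% | about 67% | about 88% |

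The signed-rank column is a paired alternative that the protocol does not plan. The table shows how readily a rate gap would be read as a method effect if one existed. It does not show that one exists.

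**The case against.** The case on the other side has real weight.

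- **H2 is not left untested.** Visits are identical in both places, and a total labor cost is normally built from an amount of labor. A reader might infer that the analysis misses H2 altogether. The text supports only that H2 is partly tested.
- **No difference between settings is documented.** A reader might infer that hourly rates, material prices or the meaning of a visit do differ between practice and laboratory. The protocol gives none of these for either place. The sentence can also be read as one prosthetist recording in both, so the confounding is by place and not necessarily by recorder.
- **Measurement costs may be partly captured.** A reader might infer that the clinical tests feeding the quantitative design go uncosted. Staff time for them can fall under labor and extra appointments under visits. Only imaging or equipment charges clearly lack a line. Which tests become inputs is also unknown until aim 2 ends, since Fig. 6 is offered as an example.
- **This is a pilot, and the article condenses a fuller protocol.** Cost is in neither the primary nor the secondary outcome list under Outcomes {12}, the trial is described as exploratory, and unit costs or log forms are usually set elsewhere.

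These points narrow the concern but do not remove it. The article states two differing component lists, and a fuller document could follow one only by departing from the other. The recording arrangement is also stated, not left open. Part of the setting difference may properly belong to the quantitative method, but the stated arrangement gives no way to tell that part from laboratory rates or overhead.

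**Conclusion.** The point stands in a limited form. H2 and its analysis share one component unchanged out of three. Socket iterations are never compared, and labor is converted to money, so H2 as defined is only partly tested. Because recording place and method coincide, the two monetary components cannot be attributed to the method rather than to the setting at any n. Visit counts are much less affected.

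These conclusions rest on the wording alone and need no numerical assumption. The rejection rates do rest on assumed inputs, and they concern labor cost only. They should not be cited as evidence that the comparison is biased or in which direction. The matter should be corrected before aim 3 costs are collected. It does not affect aims 1 and 2, the comfort comparison or any sample-size figure.

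**What to change.** 1. State one definition of cost and use it in both Specific aim 3 and the Aim 3 analysis, with the same scope for labor in each.
2. Make number of visits, number of socket iterations and labor hours the comparison that tests H2. Record them on the same form, with the same definitions, for both methods.
3. If monetary cost is also reported, value labor and materials for both methods at one common set of unit costs. Include the cost of any clinical measurement that the quantitative method finally uses as a model input.

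The cost is a common log form and about a paragraph of revised text. No participants are added. The quantitative method may look slightly less favourable once its measurement costs are counted.
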